#### Baseline characteristics

2.9.2

Baseline characteristics included year of birth, sex, body mass, highest level of education, and current city of residence.

#### Clinical outcomes

2.9.3

Clinical outcomes include AF recurrence, defined as documented symptomatic relapse or the requirement for antiarrhythmic therapy, cardioversion, or repeat ablation, assessed within three months and through twelve months post-ablation. Post-ablation complications comprise unplanned hospital readmissions, emergency department visits, thromboembolic events, major bleeding, or cardiac tamponade. Additional outcomes are all-cause mortality within twelve months, the number of cardiology or internal medicine consultations within three and twelve months (routine or symptom-driven), and additional diagnostic tests (e.g., ECG, Holter monitoring) performed during follow-up. Clinical data will be obtained from hospital records and complemented by baseline information on AF history, comorbidities, and procedure-related characteristics.

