### Blinding

2.6

Due to the nature of the intervention, it is not feasible to blind participants or healthcare professionals providing care. However, outcome assessors conducting medical record reviews for clinical endpoints (e.g., hospitalizations, cardiovascular events) will be blinded to group allocation where possible. Statistical analyses will be conducted by a researcher blinded to group assignment until completion of primary analyses. Participants will be instructed not to disclose their group allocation during follow-up assessments conducted by blinded assessors.

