#### Control group

2.7.2

Participants allocated to the control group receive standard post-ablation care as delivered at Santa Marta Hospital, which includes structured discharge instructions with written educational materials about post-ablation care, scheduled follow-up appointments at 1 month and 3 months post-discharge, open access to the cardiology clinic telephone line during working hours for clinical concerns, and a 24-h hospital telephone service for urgent medical issues. Control group participants do not receive remote monitoring between scheduled appointments.

Both intervention and control groups complete identical standardized assessments at baseline (pre-discharge) and 3 months post-ablation. The timing of data collection activities is outlined in Table 1.

**Table 1 T1:** Schedule of enrollment, interventions, and assessments for the PROMBot-HSM-AF trial.

TRIAL PERIOD		Enrollment	Post-randomization				
Timepoint	Arm	⩽ day 0	Day 0	M1	M2	M3	M12
Target window		up to day 0	day 0	30±3 d	60±5 d	90±5 d	365±14 d
ENROLLMENT							
Eligibility screen	I+C	X					
Informed consent	I+C	X					
Randomization/allocation	I+C		X				
INTERVENTIONS							
PROMBot-HSM-AF	I			X	X	X	
Standard care	C		X	X	X	X	
PRIMARY OUTCOMES (FEASIBILITY)							
Recruitment rate	I+C	X	X				
Retention rate	I+C					X	
Engagement rate	I			X	X	X	
BASELINE CHARACTERISTICS							
Demographics	I+C		X				
AF history & comorbidities	I+C		X				
Procedure-related characteristics	I+C		X				
CLINICAL OUTCOMES (HOSPITAL-REPORTED)							
AF recurrence (AAD/cardioversion/repeat ablation)	I+C			X	X	X	X
Complications (readmission, ED visit, thromboembolism, major bleeding, tamponade)	I+C			X	X	X	X
All-cause mortality	I+C						X
Cardiology/internal-medicine consultations	I+C					X	X
Diagnostic tests (ECG, Holter)	I+C			X	X	X	X
PROMs							
AFEQT	I+C		X			X	
ESC quality-indicator items (weekly, rotating)	I			X	X	X	
Symptom checklist	I			X	X	X	
Medication adherence	I			X	X	X	
BIOSIGNALS							
Body mass	I			X	X	X	
Blood pressure	I			X	X	X	
Heart rate	I			X	X	X	
Step count	I			X	X	X	
ACCEPTABILITY & USABILITY							
Patient experience (SUS, PSSUQ, interview)	I					X	
Healthcare-professional experience (SUS, PSSUQ, interview)	HCP					X	

The schedule follows the SPIRIT figure convention (34).

M, month; d, days. Arm: I = intervention; C = control; HCP = healthcare professionals.

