#### Safety monitoring protocol

2.7.4

Automated alerts are generated when patient-reported values exceed predefined clinical thresholds or when concerning symptom patterns are identified. Alert thresholds are defined as follows:

**Critical alerts (immediate response required):** Systolic blood pressure ⩾180 mmHg or less than 90 mmHg; diastolic blood pressure greater than 110 mmHg or less than 60 mmHg (32, 33); heart rate greater than 120 bpm or less than 50 bpm (29); new onset chest pain, syncope, or severe dyspnea; or three consecutive missed responses indicating potential disengagement.

**Response protocol for critical alerts:** The study nurse contacts the participant by telephone within 1 h during working hours or within 4 h outside working hours. For immediately life-threatening symptoms (e.g., chest pain suggestive of acute coronary syndrome, syncope), participants are advised to contact emergency medical services. Before escalation, the nurse verifies implausible values with the participant (confirming the technique and requesting a repeat reading) to exclude measurement error, escalating conservatively where uncertainty persists. For other concerning values, the study nurse coordinates with the treating cardiologist to determine appropriate clinical action, which may include scheduling an urgent clinic appointment, ordering diagnostic tests, or adjusting medications.

**Warning alerts (review within 24 h):** Systolic blood pressure 160 to 179 mmHg or diastolic blood pressure 100 to 109 mmHg on two or more occasions(32); heart rate 100 to 119 bpm or 50 to 60 bpm on two or more occasions(29); or reported worsening of existing symptoms.

All alerts and clinical actions taken in response are documented in both the study database and the participant’s electronic health record. Participants receive clear written instructions at enrollment specifying symptoms requiring immediate emergency medical attention vs. those that can be reported through the chatbot for routine clinical follow-up.

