#### Patient-reported outcomes and biosignals

2.9.4

Health-related quality of life will be assessed using the AFEQT, a validated, disease-specific instrument for AF (38). The AFEQT comprises 20 items across four domains (Symptoms, Daily Activities, Treatment Concerns, and Treatment Satisfaction) with an overall score (0–100) derived from the first three domains; higher scores indicate better quality of life. A change of ⩾5 points is generally considered clinically meaningful (13). The AFEQT will be administered at baseline and follow-up to assess changes in AF-related symptoms and the broader impact of management strategies on daily life. To complement the AFEQT, participants will complete brief, rotating weekly questions aligned with the ESC quality of treatment indicators (31), assessing symptom status, physical functioning, emotional well-being, cognitive function, and knowledge of AF-related risk factors. Each question will be administered once per week to minimize participant burden.

All PROMs and biosignals will be collected via the chatbot. Body mass, blood pressure, and heart rate will be self-reported daily for the first four weeks and weekly thereafter, with blood pressure and heart rate measured using a blood pressure monitor. Physical activity will be tracked as daily step counts via the smartphone pedometer. Symptoms, including palpitations, dyspnea, chest pain, dizziness/syncope, fatigue, puncture-site changes, and edema, will also be reported daily during the first four weeks and weekly thereafter. To mitigate self-report bias, participants receive standardized training on device use and measurement technique at enrollment.

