The emPOWERD-AF trial evaluated the MyAlgos platform, an application-based disease management system, and reported improvements in quality of life and favorable usability ratings from physicians (47). However, application-based approaches require installation and ongoing engagement with a standalone digital product. PROMBot-HSM-AF’s integration with WhatsApp may enhance accessibility, particularly for individuals with limited digital literacy or those reluctant to install additional health applications. Research on conversational agents in cardiovascular care has demonstrated promise. Guhl et al. (48) found that a relational agent intervention improved quality of life and anticoagulation adherence among patients with AF. More recently, Trivedi et al. (18) demonstrated high engagement with artificial intelligence-driven follow-up telephone calls after AF hospitalization, with positive effects on medication adherence and patient experience. PROMBot-HSM-AF synthesizes elements from these approaches, i.e., systematic data collection, educational support, and rule-based interactive prompts, while prioritizing rigorous feasibility assessment before scaling. This design is deliberate, with clinical escalation managed by the study team rather than the chatbot.

A critical gap addressed by PROMBot-HSM-AF is the focus on post-procedural monitoring during the highest-risk period for complications. While chronic disease management applications abound, evidence regarding digital monitoring specifically after cardiac procedures remains limited (11). The immediate post-ablation period presents distinct surveillance challenges, including distinguishing expected post-procedural symptoms from concerning complications, managing the blanking period during which arrhythmia recurrence is common and often transient, and supporting adherence to new or modified medication regimens. PROMBot-HSM-AF’s graduated monitoring schedule, intensive daily surveillance in month 1 tapering to weekly monitoring in months 2 and 3, reflects these evolving needs. Continuous self-monitoring may also heighten anxiety in AF patients (49). This risk is addressed through educational content and the informed-consent process, with reassurance regarding the expected, transient nature of early post-ablation symptoms.

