This study has several strengths. The co-creation process engaged stakeholders throughout intervention development, enhancing relevance to patient needs and clinical workflows. The mixed-methods design will provide nuanced understanding of implementation facilitators and barriers beyond feasibility metrics alone. Explicit predefinition of feasibility success criteria enables transparent interpretation of whether progression to a definitive trial is warranted. The pragmatic setting in a high-volume tertiary hospital enhances external validity to similar clinical contexts.

Several limitations merit acknowledgment. As a single-center feasibility study, findings may not generalize to healthcare systems with different organizational structures, digital infrastructure, or patient populations. The open-label design introduces potential for observation bias, though blinding of outcome assessors for objective clinical endpoints will partially mitigate this concern. The 3-month follow-up duration, while justified by the post-ablation blanking period convention, may not capture delayed recurrences or later medication transitions (e.g., discontinuation of antiarrhythmic or anticoagulant therapy).

Consistent with its feasibility design, comparisons of clinical outcomes are exploratory and should not be interpreted as evidence of effectiveness. Requiring digital literacy and Portuguese-language smartphone use introduces socio-digital exclusion, favoring younger, more digitally engaged patients over older, lower-socioeconomic patients—those with the highest AF burden yet least able to sustain digital engagement (50). Findings may therefore generalize primarily to digitally literate patients, and PROMBot-HSM-AF is intended to complement, rather than replace, usual care, with equity-oriented adaptations warranting evaluation before scale-up. Reliance on self-reported measurements introduces measurement error, including potential adherence or reporting bias (e.g., avoidance of unfavorable readings); validated devices and standardized training at enrollment will partially mitigate, though not eliminate, this risk, and no formal calibration or cross-validation against clinically measured values was performed within the study protocol. Finally, intensive daily monitoring may itself heighten symptom awareness and care-seeking, introducing a potential Hawthorne effect (51) to be considered when interpreting feasibility outcomes.

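### AF recurrence is counted from day 0, inside the blanking period and while only the chatbot arm is under symptom surveillance, so the exploratory between-arm estimate is open to differential ascertainment bias

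*Protocol article*

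**What the plan says.** All references are to the protocol article.

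- **Outcome (Section 2.9.3).** The endpoint is worded as follows: "AF recurrence, defined as documented symptomatic relapse or the requirement for antiarrhythmic therapy, cardioversion, or repeat ablation, assessed within three months". The same definition applies to a second window, which runs to month 12. The data come from hospital records. Table 1 schedules recurrence at M1, M2, M3 and M12, but its row label lists only antiarrhythmic drug, cardioversion and repeat ablation.
- **Blanking period (Discussion).** One challenge named is "managing the blanking period during which arrhythmia recurrence is common and often transient". The limitations paragraph adds: "The 3-month follow-up duration, while justified by the post-ablation blanking period convention".
- **Surveillance, chatbot arm (Sections 2.9.4 and 2.7.4).** Symptoms "will also be reported daily during the first four weeks and weekly thereafter". The nurse and cardiologist may respond to alerts with an urgent appointment, diagnostic tests or a change of medication.
- **Surveillance, control arm (Section 2.7.2).** "Control group participants do not receive remote monitoring between scheduled appointments".
- **Records and blinding (Sections 2.7.4 and 2.6, Discussion).** "All alerts and clinical actions taken in response are documented in both the study database and the" electronic health record of the participant. The blinding, applied where possible, covers "outcome assessors conducting medical record reviews for clinical endpoints". The Discussion says of observation bias that "blinding of outcome assessors for objective clinical endpoints will partially mitigate this concern".
- **Use of the result.** Section 2.10.1 plans regression models for the intervention effect on AF-related outcomes. The aims call between-group differences hypothesis-generating, to inform a definitive trial, and the Discussion names AF recurrence among that trial's endpoints.

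**The concern.** Two features combine. First, the definition counts events from a period in which the document itself regards recurrence as frequent and often passing. Second, the chance that such an event is noticed, written down and treated depends on the arm. Two of the four components, symptomatic relapse and need for an antiarrhythmic drug, are the ones most likely to follow from a symptom report or alert. The Introduction expects this: it cites earlier detection of recurrence with structured digital collection of patient-reported outcomes.

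The stated safeguard is weak for this outcome. Reviewers work from medical records that also hold the alerts. Three consecutive missed responses count as an alert too, so even a symptom-free chatbot patient may have an entry that reveals the arm. Full blinding would still not help with events that unblinded patients and clinicians detected or treated before any reviewer saw the record.

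At stake is the recurrence estimate that is meant to help design a definitive trial. It could mix intensity of observation with disease. A larger trial that kept the same definition would shrink the random error and keep the bias.

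**Working it through.** The document states no figure for recurrence by arm or for detection, so there is nothing to reproduce. The check compares the windows and then illustrates the scale under stated assumptions.

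**Windows.** The chatbot runs for 12 weeks: 12 × 7 = 84 days. The 3-month assessment is at 90 ± 5 days. Unequal surveillance thus fills nearly all of the 3-month outcome. The 12-month outcome, counted through day 365, includes every event from those first 90 days. From day 91 on, the article describes no surveillance that differs by arm.

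**Scale, by assumption.**

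- *n* = 38 per arm (Section 2.4).
- True risk *r*, equal in both arms (no effect): 15%, 20% and 45%. The Introduction gives these as patients needing evaluation at one month and up to one year. They serve only as a range and are not recurrence rates.
- Probability that a recurrence is recorded, control *d*c and chatbot *d*i: three assumed pairs. The document gives none.

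Formulas: recorded risk = *r* × *d*. Spurious risk difference = *r* × (*d*i − *d*c). Spurious risk ratio = *d*i / *d*c. SE = √[*p*c(1 − *p*c)/38 + *p*i(1 − *p*i)/38], where *p* is the recorded risk, and the 95% half-width is 1.96 × SE. The last column is the chance of a significant excess in the chatbot arm at two-sided 5% (normal approximation). With equal detection it would be about 2.5%.

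| *r* | *d*c / *d*i | Recorded, control / chatbot | Spurious difference (points) | Ratio | Half-width (points) | Bias / SE | Chance of significant excess |
|---|---|---|---|---|---|---|---|
| 15% | 0.80 / 0.95 | 12.0% / 14.25% | 2.25 | 1.19 | 15.2 | 0.29 | 4.7% |
| 15% | 0.60 / 0.90 | 9.0% / 13.5% | 4.5 | 1.50 | 14.2 | 0.62 | 9.0% |
| 15% | 0.50 / 0.90 | 7.5% / 13.5% | 6.0 | 1.80 | 13.7 | 0.86 | 13.3% |
| 20% | 0.80 / 0.95 | 16.0% / 19.0% | 3.0 | 1.19 | 17.1 | 0.34 | 5.3% |
| 20% | 0.60 / 0.90 | 12.0% / 18.0% | 6.0 | 1.50 | 16.0 | 0.74 | 10.9% |
| 20% | 0.50 / 0.90 | 10.0% / 18.0% | 8.0 | 1.80 | 15.5 | 1.01 | 16.8% |
| 45% | 0.80 / 0.95 | 36.0% / 42.75% | 6.75 | 1.19 | 21.9 | 0.60 | 8.7% |
| 45% | 0.60 / 0.90 | 27.0% / 40.5% | 13.5 | 1.50 | 21.0 | 1.26 | 23.5% |
| 45% | 0.50 / 0.90 | 22.5% / 40.5% | 18.0 | 1.80 | 20.5 | 1.72 | 39.1% |

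**A real benefit.** A true risk ratio of 0.75 would appear as 0.75 × 0.95/0.80 = 0.89, 0.75 × 0.90/0.60 = 1.13 or 0.75 × 0.90/0.50 = 1.35. In the last two cases the direction reverses.

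**Equal detection.** With *d*c = *d*i, for example 0.80 in both arms, the spurious difference is 0 and the ratio 1.00 at any *r*.

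**The case against.** The strongest reply is that this is a feasibility pilot. Its progression thresholds concern retention and engagement, the clinical contrasts are labelled exploratory, and the Discussion warns against reading them as evidence of effectiveness. That stands and limits the weight of the point. It does not remove it, because the same contrasts are meant to inform a definitive trial on recurrence.

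Controls are not unobserved. They have visits at 1 and 3 months, a clinic telephone line and a 24-hour urgent line, and Section 2.3 describes a 1-year programme with telephone consultations. Some chatbot-arm events would only be found sooner, and early treatment might prevent later ones. This too stands: it leaves the size open and the direction likely but not certain.

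Four stronger readings are tempting but unsupported:

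- **That the estimate is shown to be biased.** No detection probabilities are given, and those above are assumed. The word documented might mean ECG-confirmed, although ECGs may themselves follow alerts.
- **That the blinding claim is false.** It is hedged with where possible, and the Discussion claims only partial mitigation for objective endpoints. The full protocol may describe filtered extracts.
- **That 33% to 44% of the relevant events fall in the blanking period** (15/45 = 0.33; 20/45 = 0.44). Those are rates of needing evaluation, for recurrence or complications, from two cited sources that may differ in cohort and definition. The quotient neither counts recurrences nor measures a difference between arms.
- **That extra visits and tests in the chatbot arm are contamination.** They are utilization outcomes, and added use through alerts is partly a genuine effect of the intervention.

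Table 1 can be defended as a short row label. It still omits the component most sensitive to surveillance, and aligning it costs nothing. The article already assesses recurrence at 3 months as well as 12, but defines no post-blanking outcome.

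**Conclusion.** The point holds as a risk of differential ascertainment, not as a demonstrated bias. Blanking-period events count in both recurrence outcomes, surveillance in that window differs by design, and the mitigation offered is weak for this outcome. The likely direction is more recorded recurrence in the chatbot arm.

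The size is unknown. Under the assumed detection pairs, a null effect would appear as a risk ratio of 1.19 to 1.80 and a difference of 2.25 to 18 points. The 95% half-width is about 14 to 22 points and exceeds the assumed bias in every row, so imprecision dominates in this pilot. The figures assume no falsely recorded events, equal true risk in both arms and one detection probability per arm over the whole window.

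The plan should be changed, but the primary outcomes of recruitment, retention and engagement are untouched.

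**What to change.** 1. In Section 2.9.3, make recurrence from day 91 to day 365 the between-arm recurrence outcome, after the 12-week chatbot period. Report events to day 90 separately as early recurrence, stating that they arise under unequal surveillance. Classify by event date, since the M3 window (90 ± 5 days) spans day 90.
2. Use one definition in Section 2.9.3 and Table 1, so that symptomatic relapse is in both or in neither.
3. Give assessors record extracts with chatbot-alert entries removed. Otherwise limit the blinding claim in Section 2.6 and the Discussion to what can be kept. Removing entries hides the allocation but does not equalize detection, so it complements item 1 and cannot replace it.
4. Flag alert-triggered events and describe them. Do not present an analysis without them as a corrected estimate: it removes events from one arm only, including some that controls would also have had recorded, and so tends to bias the other way.

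**Cost.** Changes of wording and a filtered extract. M12 recurrence is already scheduled, so no visits or patients are added. Fewer recurrence events will count, which widens an already wide interval. Drug treatment begun early may carry over past day 90, so the later window reduces the problem without abolishing it.

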#### Inclusion criteria

2.3.1

Patients are eligible for enrollment if they meet all of the following criteria:
Age 18 years or older;Documented diagnosis of paroxysmal or persistent AF based on clinical assessment and coded according to the International Classification of Diseases, 11th Revision;Undergone catheter ablation for AF at Santa Marta Hospital during the study recruitment period;Able to use the PROMBot-HSM-AF chatbot independently or with caregiver assistance (Portuguese literacy sufficient to follow instructions and ability to operate a smartphone); digital literacy is assessed individually, with caregiver-assisted enrollment available for older adults willing to learn;Clinically stable at discharge, defined as absence of any complication requiring continued inpatient care or urgent reintervention (e.g., cardiac tamponade, major access-site bleeding, high-grade atrioventricular block); minor, self-limiting findings (e.g., uncomplicated groin haematoma) do not preclude participation;Provision of written informed consent.

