#### PROMBot-HSM-AF platform intervention

2.7.1

The research team will configure the PROMBot-HSM-AF chatbot and related remote monitoring platform, including definition of finite-state dialogue flows with AF-specific questions, message content, and input-validation rules. Pilot testing with 2–3 test users will also be conducted to identify usability issues and to verify delivery, latency, and data integrity. Health professionals involved in recruitment and follow-up will receive training on study procedures, including informed consent, platform registration, and use of the clinician interface to monitor incoming data.

Eligible patients undergoing AF ablation will be approached during their hospital stay. After receiving written study information, discussing questions, and providing informed consent, participants will complete a baseline assessment that will include demographics, medical history, recent clinical parameters (e.g., blood pressure and heart rate), and health-related quality of life (AFEQT, European Portuguese version) (13, 30). For participants randomized to the intervention group, PROMBot-HSM-AF will be set up before discharge by confirming WhatsApp is installed on the participant’s smartphone, registering the participant in the remote monitoring platform, linking their mobile number to PROMBot-HSM-AF, and sending a confirmatory message to verify correct enrollment. Patients (and caregivers, if applicable) will receive a brief demonstration and training, delivered by the study nurse, to ensure they can interact with the chatbot autonomously, and will also receive a leaflet with a brief explanation of the chatbot.

Participants in the intervention group will engage with PROMBot-HSM-AF via chatbot for 12 weeks. The chatbot will request self-reported health metrics (e.g., body mass, blood pressure, heart rate, step count, AF-related symptoms) and general well-being, supplemented with brief educational prompts (31). Participants who do not already own a validated blood pressure monitor will be provided with one at enrollment; device ownership is assessed during the baseline visit.

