If predefined feasibility criteria are met, findings from this pilot will inform the design of a definitive multi-center randomized controlled trial powered to detect clinically important differences in AF recurrence, complications, quality of life, and healthcare utilization. A full economic evaluation, including cost-effectiveness and budget impact analyses, would be incorporated to assess sustainability and inform health policy decisions. The qualitative findings will guide refinement of the intervention, particularly by optimizing alert thresholds, chatbot dialogue flows, and clinical monitoring interface features to minimize alert fatigue while maintaining safety, and by informing a risk-stratified approach that targets intensive digital monitoring to patients most likely to benefit (e.g., those with educational needs, poor symptom control, or elevated recurrence risk) rather than applying it uniformly.

If feasibility criteria are not met, qualitative data will illuminate specific barriers to implementation. Potential adaptations might include reduced prompt frequency, enhanced training protocols, integration with alternative messaging platforms if WhatsApp engagement proves insufficient, or simplified data collection focused on a core set of essential parameters. The modular design of PROMBot-HSM-AF enables iterative refinement of individual components based on empirical findings.

Beyond the immediate AF post-ablation context, findings may inform broader applications of chatbot-based monitoring in post-procedural care across cardiovascular and other medical specialties. The safety monitoring protocols and workflow integration strategies developed here may serve as templates for similar interventions. Furthermore, the structured PROMs and biosignal data collected through this platform will contribute to the CardioCausalAI project’s development of causal artificial intelligence models for predicting complications and optimizing clinical decision-making (48).

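### Section 2.9.3 counts emergency visits and unplanned readmissions of any cause as 'complications', so a difference between arms could reflect health-care use rather than harm

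*Protocol article*

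**What the plan says.** Section 2.9.3 (Clinical outcomes) gives the definition: "Post-ablation complications comprise unplanned hospital readmissions, emergency department visits, thromboembolic events, major bleeding, or cardiac tamponade". Table 1 has one row for it, "Complications (readmission, ED visit, thromboembolism, major bleeding, tamponade", in both arms at months 1, 2, 3 and 12. Neither place states a limit by cause, severity or relation to the procedure. The same section defines AF recurrence to include a need for cardioversion or repeat ablation, and it lists consultations and diagnostic tests as outcomes separate from complications.

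Four other places bear on how the outcome reads:

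- **Section 2.7.4 (Safety monitoring protocol).** For immediately life-threatening symptoms reported through the chatbot, "participants are advised to contact emergency medical services".
- **Discussion, limitations.** Daily monitoring may itself increase symptom awareness and care-seeking. Clinical comparisons are declared exploratory.
- **Discussion, next steps.** The definitive trial is to be "powered to detect clinically important differences in AF recurrence, complications, quality of life, and healthcare utilization".
- **Section 2.6 (Blinding).** Record review for clinical endpoints is done by assessors blinded where possible.

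**The concern.** The label is that of a safety outcome, but two of its five components are health-care contacts. As worded, an emergency visit in month 11 for an unrelated problem is a post-ablation complication. An unplanned readmission for cardioversion is both a complication and an AF recurrence.

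The contact components are also the ones the intervention acts on. Only the chatbot arm generates alerts, and the trial is open-label. If the chatbot prompts patients with worrying symptoms to be seen sooner, its arm can show more 'complications' with no more harm. If it reassures patients and averts visits, its arm can show fewer with no less harm.

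Section 1 says that between-group differences are explored to inform a definitive trial, and the Discussion names complications among that trial's outcomes. At stake are a possible false safety signal and a planning rate that overlaps with two other intended outcomes, recurrence and utilization.

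**Working it through.** The article gives no expected rate, sample size or power for complications, so there is no figure to reproduce. Two checks are possible: reading the definition against the other sections, and an expected-count illustration.

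**Reading the text**

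1. Section 2.9.3 and Table 1 agree with each other, and neither qualifies the contacts by cause.
2. Consultations are kept outside complications in section 2.9.3, while emergency visits and readmissions are placed inside. The Discussion later names complications and utilization as separate outcomes. The authors evidently regard the two as distinct, but the definition puts part of utilization under complications.
3. The alert route in section 2.7.4 exists in one arm only, so the contact components are exposed to an arm-specific cause other than harm.

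**Illustration of which components would be more frequent**

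Inputs from the article: N = 76 (38 per arm, section 2.4); 15% to 20% of patients needing evaluation in month 1 and up to 45% within a year (Introduction). These rates are only a proxy, because not every evaluation is an emergency visit or a readmission.

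Assumption, not in the article: thromboembolism, major bleeding or tamponade after enrolment in 0.5% to 3% of patients, with the same range used for both windows.

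- Patients evaluated: 76 × 0.15 = 11.4; 76 × 0.20 = 15.2; 76 × 0.45 = 34.2.
- Patients with a specific harm: 76 × 0.005 = 0.38; 76 × 0.03 = 2.28.
- Probability of no specific harm in the whole trial, (1 − p)^76: 0.995^76 = 0.68; 0.97^76 = 0.10.
- Share of affected patients with a specific harm, h/(h + u), if the two groups do not overlap:
  - month 1: 0.005/(0.005 + 0.20) = 2.4% to 0.03/(0.03 + 0.15) = 16.7%;
  - year 1: 0.005/(0.005 + 0.45) = 1.1% to 0.03/(0.03 + 0.45) = 6.3%.
- Share if every specific harm also produces a contact, h/u: month 1, 0.005/0.20 = 2.5% to 0.03/0.15 = 20%; year 1, 0.005/0.45 = 1.1% to 0.03/0.45 = 6.7%.
- Share if only half of the month-1 evaluations are emergency visits or readmissions (a further assumption; u = 0.075 to 0.10, no overlap): 0.005/(0.005 + 0.10) = 4.8% to 0.03/(0.03 + 0.075) = 28.6%.
- Break-even: with h = 3% and 15% evaluated, contacts stop being the more frequent kind only if fewer than 0.03/0.15 = one fifth of evaluations are emergency visits or readmissions.

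**Sensitivity to a single contact**

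One additional patient with an emergency visit in one arm moves that arm's proportion by 1/38 = 2.6 percentage points. That is nearly the whole of the assumed upper rate of specific harm.

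These shares show which components drive the count. They do not show what fraction of contacts is unrelated to the procedure: a readmission for a late bleed is both a contact and genuine harm.

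**The case against.** The strongest reply is that no composite is declared. The definition lists five named events, section 2.10.1 plans descriptive summaries, and each component can be reported separately. Cause coding may sit in the full protocol or the analysis plan, which are not shown. An event that appears under both recurrence and complications does no damage unless the two are added. Part of this stands: the article commits to no single complication rate. But it gives the five events one name and one Table 1 row and refers to complications as one outcome in the Discussion. A later restriction by cause would change the stated definition rather than fill in a detail.

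The alert route is also narrow. Emergency services are advised only for immediately life-threatening symptoms; other values go through the nurse and cardiologist. Controls have a 24-hour telephone line for urgent issues. The size of any chatbot effect on visits is therefore unknown, and so is its direction. The article discloses the care-seeking issue, but as something to weigh when interpreting feasibility outcomes; it does not tie it to the complication definition.

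A reader might infer more from the entry criterion, which requires "absence of any complication requiring continued inpatient care or urgent reintervention (e.g., cardiac tamponade, major access-site bleeding, high-grade atrioventricular block". It is tempting to say that true harms are stripped out before day 0, leaving an outcome that does not measure procedural harm. The article does not support this. Patients are enrolled after ablation during the hospital stay, and the intervention starts around discharge, so complications that prevent discharge precede follow-up. The criterion applies equally to both arms and leaves the randomized comparison unbiased. It does not bar every early event, since "minor, self-limiting findings (e.g., uncomplicated groin haematoma) do not preclude participation". Three of the five components are specific harms, and they are collected to month 12. The criterion affects only whom the rate describes.

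**Conclusion.** The point holds as a defect of definition and interpretability. As written, contacts of any cause count as complications. On the article's proxy rates and the assumed harm range, patients with a specific harm would make up roughly 2% to 20% of those counted at month-1 rates and 1% to 7% at the year-1 rate. If only half of month-1 evaluations are emergency visits or readmissions, the upper end rises to 29%. All these figures rest on a proxy and on an assumed 0.5% to 3%; the firm part is the wording itself.

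A reader might conclude that the outcome captures no harm, or that the chatbot arm will look more harmful. Neither follows: specific harms remain in the definition, and the article gives nothing from which to predict the direction of a difference. The supportable conclusion is that a difference in either direction could not be attributed to harm without separating the components.

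The outcome is exploratory. Recruitment, retention, engagement, the sample size and the progression thresholds do not depend on it.

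**What to change.** In section 2.9.3 and the Table 1 row:

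1. Define complications as thromboembolic events, major bleeding, cardiac tamponade, and any emergency visit or unplanned readmission judged procedure-related at the blinded record review already planned in section 2.6.
2. Report all-cause emergency visits and unplanned readmissions as a separate utilization outcome, alongside the consultations and tests already listed.
3. Show every component by arm, and say where one event also counts as AF recurrence.
4. State that events are counted from randomization, in patients who were clinically stable at discharge.

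Linking contacts to earlier chatbot alerts would be informative, but only intervention patients have alerts, so doing it within the same review would unblind the assessor. If it is wanted, someone else should do it after cause has been coded.

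The cost is a reworded outcome, an amended table row, and a modest task of coding cause from records that are already to be reviewed, with some judgement about relatedness. The downside is that complication counts will be small, possibly zero in an arm, and can only be described.
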